### Sample size calculation

Effect size and dispersion were taken from our last study of TMS against tinnitus [34]. The ratios of tinnitus distress score after treatment to tinnitus distress score at baseline are assumed to follow normal distributions with standard deviation 0.18 after taking logarithms. A relevant effect size of 0.19 logarithmic units would arise from the ratio of geometric mean scores of 80% of baseline after efficacious stimulation to 97% after sham stimulation. All three pairwise group comparisons will be conducted. Therefore the probabilities of the errors of first and second kind are Bonferroni-adjusted to significance level 0.017 and power 0.93 locally to ensure multiple level 0.05 and multiple power 0.8. Consequently the planned number of patients to be included in the study is 48, i. e. 16 in each arm. A closed testing procedure preserves the multiple significance level and power while treatments are compared at different points in time.

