### Objectives

We hypothesize that compared to sham stimulation cTBS can induce a distinctive attenuation of tinnitus distress and loudness and thus be of therapeutic value. Further aims of the study are:

• To compare the effect of cTBS on the secondary auditory cortex with its effect on the temporoparietal association cortex.

• Assessment of safety in terms of impairment in audiologic and speech-audiometric measures as well as the documentation of other unwanted side effects.

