### Outcome measures

The primary efficacy measure in the present study is the change of the tinnitus distress as measured by the TQ [45] after 4 weeks of cTBS. The TQ [45]), originally developed by Hallam et al. [49], is the most widely used, well validated and reliable inventory [50] to quantify tinnitus ditress available in German language [30,32,34,41,51-58]. It comprises 52 multi-scaled items in order to assess emotional and cognitive handicaps, penetrance of the tinnitus, hearing problems, sleep disturbances, and somatic discomfort. The TQ was used in pharmacological, behavioural and TMS studies. Pharmacological studies did not yield therapeutic effects [58,59]. Behavioural therapy yield effect sizes between 6 and 28% on the TQ [60,61]. Pilot rTMS studies reported effects sizes between 5 and 25% [34,41,52].

Secondary efficacy variables are tinnitus change [46] and the changes in BDI [47] and in the VAS for tinnitus loudness and tinnitus annoyance [46,62].

Changes regarding psychopathology will be measured using the SCL-90R [48]. Feasibility of the study will be assessed and reported together with the results.

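### SAC versus TAC is credited with local power 0.93 for a site difference the plan never specifies; with 16 per arm its power is about 0.7 for a full 0.19 log units and about 0.18 for half of that

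*Protocol article*

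**What the plan says.** The Objectives section lists as a further aim "To compare the effect of cTBS on the secondary auditory cortex with its effect on the temporoparietal association cortex". The sample size section defines one effect: the log ratio arising from "80% of baseline after efficacious stimulation to 97% after sham stimulation", rounded to 0.19. Log ratios to baseline are taken to follow "normal distributions with standard deviation 0.18 after taking logarithms". The section then says "All three pairwise group comparisons will be conducted", and for that reason the errors are "Bonferroni-adjusted to significance level 0.017 and power 0.93 locally to ensure multiple level 0.05 and multiple power 0.8". The resulting number is 48 patients, 16 per arm. Neither this section nor any other gives an expected or relevant difference between SAC and TAC, and the sidedness of the tests is not stated.

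The Data analysis section plans confidence intervals for ratios of geometric mean TQ scores at 4 and 6 weeks, from an ANOVA whose group factor has the levels SAC, TAC and PLC. The Discussion says that the finding on the best stimulation site will feed into the design of a larger trial.

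**The concern.** A local power of 0.93 corresponds to a type II error of 0.2 divided by three. That split counts SAC versus TAC alongside the two sham comparisons, so the site comparison inherits an effect size that was worked out for something else. Active against sham and one active site against another are different contrasts. If both sites work, the second will usually be smaller than the first.

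The stake is how the site result is read. The site finding is meant to inform the next trial. A reader who sees a non-significant SAC-TAC test next to a stated power of 0.93 may conclude that the two sites are alike, when the test could not have been expected to show a moderate difference.

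**Working it through.** **Inputs** (sample size section): geometric means 80% and 97% of baseline; SD of the log ratio 0.18; local level 0.017; local power 0.93; 16 per arm. Assumed: two-sided tests, all randomised patients analysed, SD pooled over the three arms (45 degrees of freedom with 16 per arm).

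**1. The plan's effect size.** ln(0.97/0.80) = 0.1927. The stated 0.19 is reproduced, for active versus sham.

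**2. The plan's patient number.** n per arm = 2 × [0.18 × (2.387 + 1.476) / 0.19]² = 26.8, so 27 per arm by the normal approximation and 28 by the pooled t. One-sided, the number is 23 to 24 (24 by pooled t). The stated 16 does not follow from the stated local level and power for any of the three pairs. This matters here because the fix must not leave 0.93 standing for the sham comparisons.

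**3. When can SAC and TAC differ by 0.19?**
- Both sites at 80%: the site difference is 0.
- One site at 80%, the other at 97%: the site difference is 0.19, but the second site is inert and its comparison with sham is null.
- All three pairs at least 0.19 apart: the best arm must reach 0.97 × exp(−2 × 0.1927) = 0.66 of baseline. The plan does not assume this. For context, the Outcome measures section says "Pilot rTMS studies reported effects sizes between 5 and 25" percent, whereas 66% is a fall of 34%.
- Second site halfway on the log scale: √(0.80 × 0.97) = 0.88 of baseline, and the site difference is 0.1927/2 = 0.096.

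**4. Power for SAC versus TAC** (noncentral t, standard error 0.18 × √(2/n), two-sided 0.017):

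| True difference | 16 per arm | 28 per arm | 29 per arm |
|---|---|---|---|
| 0.19 to 0.1927 | 0.69 to 0.71 | 0.93 to 0.94 | 0.94 to 0.95 |
| 0.095 to 0.096 | 0.17 to 0.18 | 0.33 to 0.34 | 0.34 to 0.35 |

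About 105 to 109 per arm would be needed for power 0.93 at half the effect, depending on rounding and on the normal or t calculation.

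**5. All three pairs significant together** (simulation, one site at 80%, 16 per arm). With the second site at 80, 84, 88, 92 or 97% of baseline, the probability is 0.005, 0.007, 0.009, 0.007 or 0.005, so at most about 0.01. With 29 per arm the maximum is about 0.06. With arms at 66, 80 and 97% it is about 0.45 (16 per arm) or 0.89 (29 per arm).

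**6. The two sham comparisons with 16 per arm**, both sites at 80%: about 0.7 each (0.69 to 0.71), and 0.57 for both.

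**7. Precision of the SAC/TAC ratio with 16 per arm.** The standard error is 0.18 × √(2/16) = 0.0636. At level 0.017 the half-width is 2.479 × 0.0636 = 0.158, a factor of 0.85 to 1.17. At 95% it is 2.014 × 0.0636 = 0.128, a factor of 0.88 to 1.14.

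**The case against.** A reader might infer that the site power claim is false at any sample size, because three means on one scale cannot all be exactly 0.19 apart. The documents do not support that. The power of a pair depends on its own difference. If one site is inert, SAC and TAC differ by 0.19, and that pair reaches 0.93 at about 28 per arm, as active versus sham does.

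A reader might also set 0.01 against the stated multiple power of 0.8 as a plain contradiction. That holds only if multiple power means all three pairs significant together, and the plan does not define the term. It can also mean detecting every pair that truly differs by 0.19. On that reading, simulation at 28 per arm gives 0.90 with both sites at 80%, 0.90 with one site inert, and 0.88 with arms at 66, 80 and 97%. The three-way split is then merely conservative.

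Three further points are fair. Any test has less power below its planning effect, so 0.18 at half the effect is not an arithmetic error and should not be set against 0.93 as if both referred to the same difference. The pilot range of 5 to 25% is not a ceiling for a longer, bilateral course. And no passage says that a non-significant site test will be taken as equality; most of the reporting remedy, an interval for the ratio, is already planned.

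What remains is that the site comparison shares in a stated power with no effect of its own, and that 16 per arm does not deliver that power even for a full 0.19.

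**Conclusion.** The point holds in limited form. The plan attributes local power 0.93 to a listed aim without specifying the difference to which it refers. With 16 per arm, SAC-TAC power is about 0.69 to 0.71 for a full 0.19, which within the plan's 80% to 97% range requires one site to do nothing, and about 0.18 for half of it. Correcting the patient number would repair the first figure but not the second. The figure of at most about 0.01 for all three pairs bears on the multiple power only under the all-significant-together reading.

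The figures assume SD 0.18, two-sided tests at 0.017, a pooled t and no loss of patients. One-sided tests at 0.017 with 16 per arm would give 0.79 to 0.80 for the full effect and about 0.25 for half, still well below 0.93. The half effect is an illustration chosen for this check, not a value in the plan.

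**What to change.** In the sample size section:
- Limit the power claim to the two sham comparisons and restate it as what 16 per arm delivers at level 0.017: about 0.7 each, and about 0.57 for both if both sites are at 80%. Dropping SAC-TAC from the claim while leaving 0.93 and 0.8 in place would keep figures that the design does not reach.
- State that SAC versus TAC is not powered for differences smaller than 0.19, and give its planned precision: a factor of about 0.85 to 1.17 at level 0.017, or 0.88 to 1.14 at 95%.

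In the Data analysis section:
- State that SAC versus TAC is reported as the ratio of geometric means with the interval already planned there, and that a non-significant result will not be read as equal sites.

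This is a change of wording with no change in patient number. The cost is a less favourable stated power.

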## Design and Methods

This randomised, placebo controlled study consists of 3 arms in a parallel design (Figure 1). Tinnitus distress, loudness and annoyance will be assessed before, during, and after 4 weeks of bilateral cTBS. Forty-eight patients will be randomised in an 1:1:1 ratio to either cTBS over the secondary auditory cortex (SAC), the temporoparietal association cortex (TAC) or sham stimulation (placebo: PLC).

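### Sixteen patients per arm give local power of about 0.69 at level 0.017, not the stated 0.93, so the multiple power of 0.8 is not delivered

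*Protocol article*

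**What the plan says.** All the inputs stand in the section Sample size calculation of the protocol article.

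- Dispersion: the ratios of post-treatment to baseline score "are assumed to follow normal distributions with standard deviation 0.18 after taking logarithms".
- Effect: "A relevant effect size of 0.19 logarithmic units would arise from the ratio of geometric mean scores of 80% of baseline after efficacious stimulation", set against 97% after sham.
- Family: "All three pairwise group comparisons will be conducted".
- Error probabilities: "Bonferroni-adjusted to significance level 0.017 and power 0.93 locally to ensure multiple level 0.05 and multiple power 0.8".
- Result: "Consequently the planned number of patients to be included in the study is 48, i. e. 16 in each arm".

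Design and Methods confirms the allocation: "Forty-eight patients will be randomised in an 1:1:1 ratio". The section does not say whether the tests are one- or two-sided and gives no allowance for dropout. The Objectives list the site comparison as a further aim: "To compare the effect of cTBS on the secondary auditory cortex with its effect on the temporoparietal association cortex".

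**The concern.** The difference to be detected is only slightly larger than one standard deviation (0.19/0.18 = 1.06). Sixteen per arm looks too few for power 0.93 at a level as strict as 0.017. If so, the word that links inputs to sample size is wrong, and the trial carries a power claim on its primary endpoint that it cannot meet. At power 0.93 a true difference of 0.19 would be missed 7% of the time; at 0.69 it would be missed about 31% of the time. The Data analysis section tests the time points in a fixed order and stops at the first non-significant result, so a miss at 4 weeks also closes the later tests of that comparison. The shortfall applies equally to the comparison of the two stimulation sites, and the Discussion relies on that comparison for planning a larger study.

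**Working it through.** **Inputs that reproduce.** The effect is ln(0.97/0.80) = 0.1927, stated as 0.19. The local level is 0.05/3 = 0.0167, stated as 0.017. The local power is 1 − 0.2/3 = 0.933, stated as 0.93. The sample size is the step that does not reproduce.

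**Sample size for the stated power.** Two independent arms, two-sided 0.017, power 0.93, normal approximation:

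n = 2 × (SD/δ)² × (z₁ + z₂)² = 2 × (0.18/0.19)² × (2.387 + 1.476)² = 26.8, so 27 per arm.

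With the noncentral t distribution, the smallest n is 28 using the pooled three-group residual and 29 using a separate two-group t-test. The total is 84 to 87 patients, or 81 by the normal approximation, against 48.

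**Power at 16 per arm.** The noncentrality is (0.19/0.18) × √(16/2) = 2.99. The pooled residual has 3 × 16 − 3 = 45 degrees of freedom at one time point; a two-group t-test has 2 × 16 − 2 = 30.

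| Test, 16 per arm, δ = 0.19, SD = 0.18 | Pooled, 45 df | Two-group, 30 df | Normal |
|---|---|---|---|
| two-sided 0.017 | 0.693 | 0.676 | 0.725 |
| one-sided 0.017 | 0.785 | 0.774 | 0.807 |
| two-sided 0.05, no adjustment | 0.832 | 0.824 | 0.847 |
| one-sided 0.05, no adjustment | 0.902 | 0.898 | 0.910 |

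With the unrounded effect 0.1927, the first row becomes 0.707, 0.690 and 0.739. No row reaches 0.93. For 16 per arm to give 0.93 at two-sided 0.017, the standard deviation would have to be about 0.135 to 0.14 instead of 0.18.

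**Multiple power.** Splitting the type II error over three pairs guarantees at least 1 − 3 × 0.07 = 0.79, roughly the stated 0.8, if each local power is 0.93. With local power 0.693 the same bound is 1 − 3 × 0.307 = 0.08. Simulated probabilities with 16 per arm, two-sided 0.017 and 45 df:

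- Both active arms 0.19 better than sham, both comparisons with sham significant: 0.55 (0.57 with 0.1927).
- Neighbouring arms 0.19 apart, so that all three pairs differ, all three significant: 0.43.

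**What 16 per arm can detect.** Solving for δ at local power 0.93 (two-sided 0.017, 45 df) gives 0.254 log units. With sham at 97% of baseline, that puts the active arm at 0.97 × exp(−0.254) = 0.75 of baseline, not 0.80.

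**SAC versus TAC.** The arm sizes, SD and level are the same, so power is 0.69 for a true difference of 0.19. For half of that, 0.095, it is 0.17.

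**The case against.** The strongest defence is that the section does not fix how the inputs are to be read. Sidedness is unstated, but a one-sided test gives at most 0.79 with the t distribution and would still need 24 to 25 per arm. Reading 0.18 as the standard deviation of a between-arm difference would give 14 per arm by the normal formula, but the text attaches it to the ratio of post-treatment to baseline score. The closed procedure concerns time points and does not relax 0.017. If both sites work, the probability that at least one active arm beats sham is about 0.83, which is close to 0.8. A type II error split over three pairs, however, aims at detecting every true difference, not at least one. None of these readings restores 0.93.

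Some stronger readings are tempting but not supported.

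- A reader might infer that multiple power over three pairs cannot exist, because at least one pair is null if one or both sites work equally at 80%. A true null carries no type II error, so the split validly bounds the chance of rejecting all false nulls, whether two or three pairs differ. The section also never says that both sites sit at 80%. The fault lies in the sample size, not in the concept.
- A reader might infer how 16 arose. It lies close to a two-sided 0.05 calculation with power 0.80 (15 by the normal formula) and equals a one-sided 0.017 calculation with power 0.80 (16 by the normal formula). The document cannot decide between them.
- A reader might infer that SAC versus TAC must be demoted to estimation, or multiple power redefined on two pairs. Those are design choices that the arithmetic does not force.

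It is also fair to say that this is a phase II trial meant to inform a larger one. That makes a modest power acceptable; it does not make a misstated power correct.

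**Conclusion.** The point holds. The article states every input and the result, and they contradict each other, so this is not a detail left to a fuller document. At 16 per arm local power is about 0.69, some 24 percentage points below the stated 0.93, and the chance that both active arms beat sham is about 0.55 when both differ from it by 0.19. This rests on the plan's own SD and effect, two-sided testing (an assumption), normal log ratios with equal variance, the pooled three-group residual at a single time point, and 16 analysable patients in each arm. Efficacy is analysed per protocol with no stated allowance for losses, so any exclusion would lower the power further; the document gives no rate from which to say by how much.

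**What to change.** Keep 48 patients and correct the section Sample size calculation:

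- Remove the claims of local power 0.93 and multiple power 0.8.
- State that 16 per arm give local power of about 0.69 at level 0.017 for a difference of 0.19 log units, and a probability of about 0.55 that both active arms beat sham when both differ from it by 0.19. Use 0.19 throughout, or 0.1927 throughout (then about 0.71 and 0.57), so that the figures agree.
- State the detectable difference at local power 0.93: about 0.25 log units, i.e. active at about 75% of baseline against 97% for sham.
- State the sidedness assumed.
- Note that SAC versus TAC has the same power: about 0.69 for a true difference of 0.19 and about 0.17 for half of it.

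The change is to wording only and needs no extra patients. Its cost is a less favourable stated power. Keeping the 0.93 claim would instead mean about 28 to 29 patients per arm.

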### Data analysis

The geometric mean tinnitus score (TQ) in percent baseline will be compared between the three groups after the full treatment course of 4 weeks after the first stimulation, after 6 weeks, as well as 28 and 56 weeks after the first cTBS treatment in that prespecified order, as we expect effects sizes to have that order. If one group comparison is not statistically significant, the following comparisons are rated as not significant too. The confidence intervals for ratios of geometric means of tinnitus scores at 4 and 6 weeks will be computed from an analysis of variance (ANOVA) with factors *group *(SAC, TAC, PLC) and *time *(4 and 6 weeks) and the *group*time *interaction. Further ANOVAs of TQ with the between subject factor *group *will be carried out after 8, 28, and 56 weeks after the first treatment. Their residual variances are expected to differ. The longitudinal course of the stimulation effect will be described using all TQ measurements, including measurements at 2 and 16 weeks. Secondary efficacy measures will be analysed similarly. Only the tinnitus change cannot be divided by a baseline value and will be analysed by ordinal logistic regression as it is ordinal. The daily measurements on visual analog scales will be shown in diagrams. Confidence interval computations will assume normality of logit-transformed VAS. The routinely sampled safety data will all be plotted for each patient and will be used to quantify intensity and duration of adverse effects should such occur. Data analysis will be performed in the Department of Medical Biometry of University Hospital of Tübingen using JMP 7.0 (SAS Institute Inc.) after imputation with SPSS 17.0 (SPSS Inc.).

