### TMS and tinnitus

Repetitive transcranial magnetic stimulation has recently been adopted to strengthen the concept of focally increased cortical excitability as a pathophysiological mechanism of tinnitus perception. Initially, it was shown that a high-frequency (10 Hz) rTMS induced 'virtual' lesion of temporoparietal cortical areas can transiently reduce tinnitus [26,27]. Further studies indicated that the effect size was negatively correlated with the tinnitus duration [28,29]. On the basis of these data, it has been proposed that a rTMS-induced reduction of hyperactivity of these cortical areas could yield beneficial effects for patients with chronic tinnitus [27]. To test this notion, low frequency rTMS was applied to areas of the temporoparietal cortex showing tinnitus-related hyperacitivity. Immediately after this intervention, tinnitus loudness was reduced for up to 30 min. The degree of reduction was dose dependent, and negatively correlated with tinnitus duration [11]. Several small clinical studies indicate that repeated application of low-frequency rTMS up to 2 weeks may have lasting ameliorating effects on chronic tinnitus [30-37]. However, the effect size was mostly moderate and interindividual responses as well as effect duration were highly variable. Further studies are needed to assess the clinical relevance of rTMS treatment in tinnitus and to identify the optimal stimulation paradigms as well as the most effective stimulation target site. Recently, continuous theta burst stimulation (cTBS) has been put forward as a modified rTMS paradigm [38] that reduces cortical excitability by applying three pulses at 50 Hz repeated every 200 ms over 40 s [38,39] at an intensity of 80% active motor threshold (AMT). For clinical purposes cTBS appears to be an applicable technique due to its low intensity, short duration, and similar efficacy [40]. In a first case report we demonstrated that cTBS is an effective approach to treat tinnitus [41].

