#### Inclusion criteria

• Written informed consent

• Age: between 18 and 75 years

• Chronic tinnitus since at least 6 month, but not more than 5 years.

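### Every TQ model uses baseline only as a divisor; adding log baseline TQ as a covariate would gain some precision at almost no cost

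*Protocol article*

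**What the plan says.** The primary outcome is a change score. Outcome measures states: "The primary efficacy measure in the present study is the change of the tinnitus distress as measured by the TQ", taken after four weeks of stimulation. Data analysis gives it a form: "The geometric mean tinnitus score (TQ) in percent baseline will be compared between the three groups". For 4 and 6 weeks, the confidence intervals "will be computed from an analysis of variance (ANOVA) with factors" group, time and their interaction. The later ANOVAs have group as the only between-subject factor and "will be carried out after 8, 28, and 56 weeks after the first treatment". No TQ model includes a baseline TQ term.

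The Sample size calculation section uses the same quantity. Ratios of post-treatment to baseline scores "are assumed to follow normal distributions with standard deviation 0.18 after taking logarithms", and the target difference is 0.19 log units. Table 1 shows TQ measured at V1, the baseline visit. Apart from consent and age, the one inclusion criterion is "Chronic tinnitus since at least 6 month, but not more than 5 years", so no minimum TQ is set.

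**The concern.** Comparing log(TQ/baseline TQ) between groups is the same as modelling log TQ with the coefficient of log baseline held at 1. A questionnaire score is measured with error. If its log variance is similar at both visits, the true coefficient equals the correlation r, which is below 1. The unmodelled part, (1 − r) times log baseline, then stays in the residual. It widens the confidence intervals, and it shifts the estimate whenever the arms differ by chance at baseline.

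With 16 patients per arm, such differences will not be negligible. The trial also has little precision to spare: on its own inputs, power per comparison is well below the stated local 0.93 (see the working).

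**Working it through.** **Inputs from the protocol article.** Effect d = 0.19 and SD of the log ratio 0.18; local two-sided level 0.017 and local power 0.93; 16 per arm in three arms (all from Sample size calculation). The correlation r between log TQ at baseline and at follow-up is not given, so it is an assumption and a range is shown.

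**The plan's own figure.** By normal approximation, n per arm = 2 × (0.18/0.19)² × (2.387 + 1.476)² = 2 × 0.8975 × 14.92 = 26.8, so 27. With t-tests it is 28 to 29. The stated 16 is not reproduced; that is a separate matter, but it sets the reference power. At 16 per arm the noncentrality is 0.19/(0.18 × √(2/16)) = 2.986. With 45 residual df the critical value is 2.479 and the power is 0.693 (0.725 by normal approximation).

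**Effect of adjustment.** Let s be the log-SD, equal at both visits.
- Log-ratio analysis: variance = 2(1 − r)s².
- Adjusted analysis: variance = (1 − r²)s².
- Ratio = (1 + r)/2, so the reduction is (1 − r)/2.

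The adjusted SD is 0.18 × √((1 + r)/2). Power uses the noncentral t with 44 df.

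The SD of 0.18 also ties r to the spread of baseline scores: 0.18² = 2(1 − r)s², so s = 0.18/√(2(1 − r)). The central 95% of baseline scores then spans a factor of exp(2 × 1.96 × s).

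| r | Variance reduction | Adjusted SD | Power, 16 per arm | n per arm for 0.93 (t) | s | 95% baseline range |
|---|---|---|---|---|---|---|
| none (as planned) | – | 0.180 | 0.693 | 28 | – | – |
| 0.5 | 25% | 0.156 | 0.828 | 22 | 0.18 | 2.0-fold |
| 0.7 | 15% | 0.166 | 0.772 | 24 | 0.23 | 2.5-fold |
| 0.8 | 10% | 0.171 | 0.745 | 26 | 0.28 | 3.0-fold |
| 0.9 | 5% | 0.175 | 0.718 | 27 | 0.40 | 4.8-fold |
| 0.955 | 2% | 0.178 | 0.704 | 28 | 0.60 | 10.5-fold |

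The large gains therefore require a narrow baseline population. With no minimum TQ at entry, a wider spread is more likely, and that points to the lower rows.

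**Cost of estimating the slope.** The table counts the lost df but not the variance added by chance imbalance in the covariate. On average that is a factor of about 1 + 1/(45 − 2) = 1.023. It roughly cancels the 2% gain at r = 0.955 and leaves about 1 − 0.95 × 1.023 = 3% at r = 0.9.

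**Unequal variances.** If the follow-up log-SD is k times the baseline log-SD, the variance ratio is k²(1 − r²)/(1 + k² − 2rk). For k = 0.8 and r = 0.5 it is 0.571, a 43% reduction. For k = 1.2 and r = 0.8 it is 0.997, under 1%.

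**Chance imbalance.** A one-standard-error difference in log baseline between two arms is s × √(2/16). It shifts the unadjusted contrast by (1 − r) times that amount: 0.032, 0.025 or 0.014 log units for r = 0.5, 0.7 or 0.9. That is about 17%, 13% or 7% of the 0.19 target.

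**The case against.** The strongest reply is that nothing here is invalid. Baseline is used, the log-ratio contrast is unbiased over randomisations, and the analysis matches the quantity on which the trial was sized. All of that stands, and it limits the point to efficiency and conditional bias. It is also fair that r = 0.5 or 0.7 sits badly with a wide range of baseline scores; the table shows this. What remains is that the article itself names the model terms, so the omission is a stated choice, and the alternative uses data already in hand.

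Three stronger readings are tempting and should not be drawn.

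- *Patients with low baseline scores dominate the comparison.* A 4-point fall is ln(6/10) = −0.51 from a score of 10 but ln(56/60) = −0.07 from 60. Yet geometric means weight patients equally, and the sample size section assumes one SD on the log scale. Simulated on that basis (assumed TQ mean 40, SD 15), the lowest baseline quartile contributes 25% of the residual sum of squares, its fair share. It reaches about 64% only if error is additive (assumed SD 7 points), which the documents do not state. A covariate would not cure unequal variance in any case.
- *Tinnitus duration should be a second covariate.* The Background says: "Further studies indicated that the effect size was negatively correlated with the tinnitus duration". That concerns the size of the stimulation effect and so suggests effect modification. It does not show that duration would sharpen a main-effects comparison.
- *The randomisation was unstratified.* The Randomization section mentions permuted blocks and no strata, but a condensed article's silence does not settle this.

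**Conclusion.** The point holds as a modest, inexpensive improvement. The planned TQ analyses fix the slope on log baseline at 1 and so give up precision whenever the true slope differs from 1. Under equal log variances the loss is between about 2% and 25% of residual variance for r from 0.955 down to 0.5, and power per comparison would rise from 0.69 to between 0.70 and 0.83. The correlation is an assumption throughout. Given the SD of 0.18 and no minimum entry score, a reduction of about 2% to 10% (power about 0.70 to 0.745) is the likelier range, and at the top of the r range the net gain is essentially nil.

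A reader might infer that adjustment repairs the shortfall in power. It does not: at every r in the table, 0.93 still needs 22 or more per arm. Nor does the omission make the planned comparison wrong.

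**What to change.** Add log baseline TQ as a covariate to every TQ model: the group-by-time model at 4 and 6 weeks and the group-only models at later visits. Either log TQ or the log ratio may be the response, since the group contrast is identical once log baseline is in the model. The contrast remains a ratio of geometric means, so the reported quantity and the 0.19 target do not change.

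Keep the logarithm of the score itself. Adding 1 to each score before taking logs would change the ratio being reported. Inspect the residual spread at low baseline scores as a model check.

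The cost is one line in the analysis plan and one residual degree of freedom (45 to 44 for a single-visit comparison). No extra data are needed, because TQ is already collected at V1. The change should be fixed before unblinding.

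### The time-ordered testing rule does not say whether its gate runs within each pair or across all three pairs, week 8 has no place in the order, and power is said to be preserved at time points where it cannot be

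*Protocol article*

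**What the plan says.** The Sample size calculation section sets up two layers of multiplicity.

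- **Across pairs:** "All three pairwise group comparisons will be conducted". The comparisons are SAC against sham, TAC against sham, and SAC against TAC, each at a Bonferroni-adjusted level of 0.017 with local power 0.93.
- **Across time:** "A closed testing procedure preserves the multiple significance level and power while treatments are compared at different points in time".

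The planning means are "80% of baseline after efficacious stimulation to 97% after sham stimulation", so there are two values for three arms.

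The Data analysis section then orders the tests: week 4 first, then "after 6 weeks, as well as 28 and 56 weeks after the first cTBS treatment in that prespecified order", because effect sizes are expected to follow that order. The stopping rule is "If one group comparison is not statistically significant, the following comparisons are rated as not significant too". Weeks 4 and 6 share one analysis of variance. Further ones with the factor group are to "be carried out after 8, 28, and 56 weeks after the first treatment". Weeks 2 and 16 are the only ones named as extra measurements for the description of the longitudinal course.

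**The concern.** Three things in these two sections do not fit together.

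1. The stopping rule speaks of one group comparison, but three are made at each time, and no order among the pairs is given. On a common gate, a single failed pair at week 4 closes weeks 6, 28 and 56 for every pair. On a gate within each pair, it closes them for that pair only.
2. Week 8 is analysed alongside weeks 28 and 56 but is missing from the order, so its status is open.
3. A fixed sequence protects the significance level. It cannot protect power at later steps, because a later step counts only if every earlier one succeeded.

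The Follow-up assessments section makes duration of effect a purpose of the later visits. These rules decide whether any lasting effect may be called significant.

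**Working it through.** **Inputs.** From Sample size calculation: effect 0.19 on the log scale (check: ln(0.97/0.80) = 0.193), SD 0.18, local level 0.017, local power 0.93, 16 per arm. Not in the document and therefore assumed: two-sided tests, t-tests with SD pooled over the three arms, equal within-patient correlation of 0.5 to 0.8 between visits, and a constant effect over time unless stated.

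**The plan's own figures.** The Bonferroni arithmetic holds: 0.05/3 = 0.0167 and 1 − 0.2/3 = 0.933. The 16 per arm does not follow from it:

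- n per arm = 2 × 0.18² × (2.387 + 1.476)² / 0.19² = 26.8, so 27 by the normal formula and 28 by the t distribution with pooled SD.
- With 16 per arm the noncentrality is 0.19 / (0.18 × √(2/16)) = 2.99, and the critical t on 45 degrees of freedom is 2.48. Power is 0.69 (0.725 by the normal formula).

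This is a separate sample-size error. It matters here because the cost of the gate has to be shown apart from it.

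**Common gate.** If each of three arms has one of two means, at least two arms share a mean and at least one pair is null. If both sites work, that pair is SAC against TAC. If one works, it is the other site against sham. The null pair passes with probability 0.017, so all three pass with at most that probability, whatever the sample size. By simulation:

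| Scenario at week 4 | 16 per arm | 28 per arm |
|---|---|---|
| Both sites at 80% | 0.004–0.005 | 0.010 |
| One site at 80% | 0.004 | 0.011 |

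**Gate within each pair.** Probability that an active-against-sham pair with a constant 0.19 effect is still significant at each step:

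| Per arm | Correlation | Week 4 | Week 6 | Week 28 | Week 56 |
|---|---|---|---|---|---|
| 28 | 0.5 | 0.93 | 0.88 | 0.84 | 0.81 |
| 28 | 0.8 | 0.93 | 0.90 | 0.88 | 0.86 |
| 16 | 0.5 | 0.69 | 0.55 | 0.46 | 0.40 |
| 16 | 0.8 | 0.69 | 0.60 | 0.55 | 0.51 |

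The rows with 28 per arm isolate the gate. Starting from the stated 0.93, it costs 0.93 − 0.86 = 0.07 to 0.93 − 0.81 = 0.12 by week 56. In the rows with 16 per arm, the step from 0.93 down to 0.69 comes from the sample size, and only the fall after week 4 comes from the gate. A constant effect is the favourable case, since the protocol expects effects to decline. With an assumed decline to 90, 70 and 50% of the week-4 effect, 28 per arm leaves 0.26 to 0.31 at week 56, part of which is the smaller effect itself.

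**Week 8.** The order is 4, 6, 28, 56. The analysis list is 4 and 6, then 8, 28, 56. If week 8 were a confirmatory family outside the gate at 0.017 per pair, the probability of any false rejection at weeks 4 or 8 under the global null would be 0.082, 0.076 and 0.071 at correlations 0.5, 0.7 and 0.8.

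**The case against.** The strongest reply is that the plan already intends a gate within each pair. The level is split over pairs by Bonferroni, and the closed procedure is described for time points only. A single common chain would need no split. On that reading a failed SAC-against-TAC test closes only later tests of that pair. This is the better fit to the 0.017, and it stands. It does not settle the matter, because the rule as worded names no pair and literally permits the common gate. The two readings differ between almost no chance and a fair chance of a follow-up claim.

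A reader might infer four stronger things that the document does not support.

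- **That the trial cannot claim a lasting effect.** This holds only on the common-gate reading.
- **That SAC against TAC is null by plan.** The protocol gives 80% after efficacious stimulation and never says that both sites reach it. The comparison of sites is an aim, and the local power of 0.93 is meant to cover that pair too. Three spaced means (steps of 0.19) would let all three pairs pass week 4 with probability about 0.43 at 16 per arm, but no third mean is given.
- **That week 8 breaks the 0.05 level.** The text does not call week 8 confirmatory, and the description over time uses all TQ measurements. Inflation is possible, not shown.
- **That the gate takes power from 0.93 to about 0.5 or below.** Most of that fall is the sample size.

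It is also fair to say that both readings of the gate hold the multiple level, and that the later weeks are secondary in a phase II trial meant to inform a larger study.

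**Conclusion.** The point holds in three parts.

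- **The gate is undefined.** On its literal reading, with the two planning means, weeks 6, 28 and 56 are opened with probability about 0.005 at 16 per arm (0.010 at 28), whether one site or both work.
- **Week 8 is inconsistent between the two lists.** It would raise the error for weeks 4 and 8 together to about 0.07–0.08 only if it were treated as confirmatory and ungated.
- **The power claim is wrong for weeks 6, 28 and 56.** Even from a true 0.93 at week 4, about 0.81 to 0.86 remains at week 56 with a constant effect. With 16 per arm the chain runs from about 0.69 to about 0.40–0.51, where the low start is the separate sample-size error.

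The results rest on two-sided tests and on assumed correlations. The bound of 0.017 for the common gate needs no correlation, only that each arm has one of the two planning means. The primary comparisons at week 4 are not touched by the gate.

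**What to change.** Change three places in the text.

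1. In Data analysis, state that the time order runs separately within each pair (SAC against sham, TAC against sham, SAC against TAC), each at 0.017, and that a failure in one pair does not stop another.
2. Give week 8 a status: either a place in the order between weeks 6 and 28, or a descriptive label like weeks 2 and 16. A place in the order adds one more step that weeks 28 and 56 must wait for. The descriptive label does not.
3. In Sample size calculation, limit the closed-testing sentence to the significance level, and let any power statement apply to week 4 only.

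This costs a few sentences, with no new data and no change to the visits. It does not repair the shortfall of 16 per arm against the stated local power, which has to be dealt with separately.
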